
Response rates will be tabulated by healthpost and by PSP area. Reasons for non-response will be tabulated.

Survey analyses will use sampling weights calculated as the inverse of the sampling probabilities, with robust standard errors to take account of cluster sampling using svy commands in Stata.

Coverage:

Coverage of IPTc (the proportion with 0,1,2 and 3 treatments received) will be estimated using svy commands in Stata to weight the sample according to the survey design, using sampling weights calculated as the inverse of the probability of selection for a given household in each healthpost. The following measures of IPTc coverage will be calculated:

Overall coverage

Separate estimates of coverage for those with doses confirmed by their DSS card, and those without.

Number of courses received by age group. Of particular interest is the comparison of children over 5 years with those under 5.

Summary of reasons for missed doses.

Summary of problems with administration of the most recent dose.

Attendance at school and missed classes due to administration in November.

Coverage will also be analysed in relation to socioeconomic status and other factors:
SES obtained from household assets

Self-assessment of relative wealth, for comparison with the asset-based indicator

Equitability of coverage for IPT and ITNs

Distance of village to health facility (from GPS coordinates)

Caregiver’s level of education.

ITN Coverage:

Coverage indicators for ITNs (defined as intact or impregnated net) will be calculated:

Overall coverage defined as ownership and as use the previous night.

Separate estimates of coverage by age group (compare children over 5 years with under 5s).

Equitability of coverage for IPT and ITNs

Prevalence of parasitaemia:

For parasitaemia the following measures will be calculated:

Prevalence of *P.falciparum* asexual parasitaemia

Prevalence of *P.falciparum* gametocyte carriage

Prevalence by intervention area (PSP/non-PSP)

Prevalence according to ITN use

Prevalence of infection with *P. malariae* and *P.ovale*

The prevalence ratio between SMC and control areas will be estimated using survey poisson regression with a robust standard error to reflect the cluster sampling design. Interaction terms will be included to compare efficacy between age groups and to determine if there is any evidence of synergistic interaction between PSP and ITNs.

Prevalence of anaemia:

Prevalence will be calculated by intervention area (PSP/non-PSP) and according to ITN use (ITN defined as intact or impregnated net) and by SES group, for each age group. Interaction by age group will be assessed. Two endpoints will be considered, moderate anaemia (Hb<11 g/dL), and severe anaemia (Hb<6 g/dL). Analysis methods are similar to those for prevalence of parasitaemia.

Haemoglobin concentration:

Haemoglobin concentration will be analysed by normal regression, to estimate differences in mean Hb concentration in PSP and control areas, and by age group.

Drug resistance markers:

Prevalence of the following resistance-associated genotypes will be tabulated

pfdhfr-51, 59, 108 triple mutant (resistance to pyrimethamine)

pfdhps-437 and pfdhps-540 mutations (resistance to sulfadoxine)

Quadruple mutant (DHFR triple mutant plus DHPS 437 mutation)

pfcrt CVIET, pfmdr1 86Y, and pfmdr1 184F mutations associated with resistance to amodiaquine

The prevalence of resistant genotypes will be estimated in two ways. Firstly the proportion of slide-positive samples that are positive for the marker will be calculated. Secondly, the overall prevalence of the marker will be estimated, this is calculated as P1xP2 where P1 is the prevalence of asexual parasitaemia and P2 is the proportion of those who had parasitaemia, who were positive for the resistance genotype. A 95%CI for (P1xP2) is given by P1P2/EF to P1P2xEF where EF=exp{1.96x√[(1/P1)2V(P1)+ (1/P2)2V(P2)]}, where V(P1) is the variance of the survey estimate of the prevalence, obtained from the output from Stata svy commands, and V(P2) is the variance of the proportion of the n *P.falciparum*-positive samples that were positive for the mutation, [P2(1-P2)/n].

The prevalence (both measures) will be compared between PSP and non-PSP areas in each year of the study. To compare the overall prevalence measures, if the prevalence in PSP areas is a= P1P2 and in control areas b= P3P4, with V(a) and V(b) V(a)= P22V(P1) +P12V(P2) and V(b)= P42V(P3) +P32V(P4), for the difference a-b, se(a-b)= √[V(a)+V(b)], so the 95%CI for the difference is (a-b)+/-1.96*se(a-b), and for the P-value we can use the z-test with z=(a-b)/se(a-b). For the risk ratio RR=a/b, need to work on a log scale again,

se(log(RR))=√ [(1/a2)V(a)+(1/b2)V(b)] = √[V(P1)/P12 +V(P2)/ P22 + V(P3)/P32 +V(P4)/ P42]

95%CI logRR+/-1.96xse(logRR), and z test, z=log(RR)/se(log(RR)).

Serology:

The prevalence of antibodies to apical membrane antigen (AMA)-1 and to merozoite surface protein 1 (MSP-119) will be estimated in PSP and control areas in 2009, and by age group. The data will be used to investigate evidence for changes in transmission in the recent past by fitting a model for the seroconversion rate to the age-prevalence profile, in each district and in PSP and non-PSP areas. Seroconversion rates will be estimated using a superinfection model (S Bosomprah PhD thesis).

Adverse drug reactions:

Severe and serious cases of suspected adverse drug reactions reported through the pharmacovigilance system will be assessed for association with PSP drugs by a safety review panel. The incidence will be estimated in relation to the number of children treated. The incidence of all reported cases within 10 days of PSP rounds, from yellow forms collected from health facilities, will be tabulated by month and year and by age and gender, and by symptom type. Rates will be estimated in relation to the number of treatments administered.

1. * NA = Not Appropriate [↑](#footnote-ref-2)
2. 1 Centre d'études statistiques appliquées à la médecine [↑](#footnote-ref-3)

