***Anemia and parasitemia prevalence endpoints:***Assuming a coefficient of variation between clusters of 0.25, this sample size indicate above will give 80% power (using a 5% significance level and allowing for 20% loss to follow up) to detect, in the first year of the study, a halving in the prevalence of a) anemia (hemoglobin<8 g/dL) which has an expected prevalence of 15% in control clusters); b) parasitemia prevalence (expected prevalence of 20% in control clusters). Combining the data for the three years (strata) will give power for smaller magnitude effects; c) prevalence of fever with parasitaemia in children.

***Prevalence of SP resistant parasite genotypes:***Another endpoint of interest is the prevalence of drug resistant genotypes in December. We will determine the prevalence of the DHFR triple mutation and the DHPS (codon 437) mutation associated with resistance to pyrimethamine and sulfadoxine respectively. We have calculated power for non-inferiority, to show that IPT does not make SP resistance worse, and the power to detect an important reduction in prevalence of SP resistance genotypes associated with sIPTc.

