**- Incidence of hospital cases of severe malaria**

The area is served by two small district hospitals (Bambey and Mbour). There are referral hospitals at Thies and Fatick. Hospital admissions with severe malaria (i.e. malaria that presents with life threatening conditions, including coma, severe anaemia, renal failure, respiratory distress syndrome, hypoglycaemia, shock, spontaneous haemorrhage, and convulsions) will be documented. Records will be kept of admission of study children. Physicians and nurses based at these facilities will check whether children with severe malaria live in the study area, and record carefully details from their malaria ID card, and clinical biochemical and parasitological data will be recorded on a Case Report Form, with treatment details, final diagnosis using standard WHO criteria, and outcome.

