**- Prevalence of anemia and parasitemia**

Hemoglobin measurements using a *Hemocue* machine, and finger prick sampling for thick smears for parasite density determination, will be done once in each stratum, at the end of transmission season, in a sub-sample of children. For these endpoints, 150 children will be randomly selected from each cluster. A slide will be declared negative only after 200 high power fields are examined without finding a parasite. A second independent laboratory technician will reread all collected slides. If parasite densities recorded by the two readers differ by more than 30%, a third senior laboratory technician will be asked to adjudicate. Anemia will be defined by hemoglobin level of less than 8 g/dL.

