**Statistical Analysis Plan**

**Dec 2013**

Outcomes:

All-cause mortality in children aged 3-59 months and 60-119 months (primary outcome)

Cause of deaths in 13 health post areas where verbal autopsies will be performed

Incidence of RDT-confirmed malaria

Incidence of malaria (confirmed and unconfirmed)

Incidence of severe malaria (admission to hospital with primary diagnosis of malaria)

IPTc Coverage: proportion who received 1,2 and 3 courses of IPTc, and the proportion who received no IPTc, each year of the study

ITN Coverage

Prevalence of parasitaemia at the end of each transmission season

Prevalence of gametocyte carriage

Prevalence of anaemia (moderate: Hb<11g/dL and severe: Hb<6g/dL)

Mean haemoglobin concentration

Prevalence of drug resistance markers

Serology: prevalence of antibodies to CSP, MSP1 and AMA1

Costs of IPTc delivery: financial and economic costs to the provider

Incidence of serious adverse drug reactions

Baseline characteristics:

Characteristics of the 6 implementation zones will be tabulated, including DSS estimates of population size of children and including all age groups, bednet use recorded in each DSS round in children under 10 years and in older age groups, the mean distance to the nearest health facility, socio-economic status, religion and ethnicity.

Mortality rates:

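### The SAP omits the protocol's anaemia endpoint (Hb below 8 g/dL) and labels as severe malaria any admission with malaria as the primary diagnosis, without giving a reason for either change

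*Combined protocol and SAP*

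**What the plan says.** **Anaemia, protocol.** The outcome section (Prevalence of anemia and parasitemia) states: "Anemia will be defined by hemoglobin level of less than 8 g/dL". Section 2.3 uses the same cut-off for power: "anemia (hemoglobin<8 g/dL) which has an expected prevalence of 15% in control clusters". It says that the survey sample "will give 80% power (using a 5% significance level and allowing for 20% loss to follow up) to detect", in year 1, "a halving in the prevalence of" that endpoint.

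**Anaemia, SAP.** The section Prevalence of anaemia closes the set: "Two endpoints will be considered, moderate anaemia (Hb<11 g/dL), and severe anaemia (Hb<6 g/dL". The SAP's Outcomes list names the same two cut-offs. Hb below 8 g/dL appears nowhere in the SAP, and no power is given for the two new cut-offs. Mean haemoglobin is analysed separately by normal regression.

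**Severe malaria, protocol.** The section on hospital cases of severe malaria counts admissions for malaria with life-threatening manifestations such as coma, severe anaemia or shock. Clinical, biochemical and parasitological data go on a case report form, with "final diagnosis using standard WHO criteria, and outcome".

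**Severe malaria, SAP.** The Outcomes list has "Incidence of severe malaria (admission to hospital with primary diagnosis of malaria". It sets no severity criterion, does not mention WHO criteria and does not ask for a positive test. The outcome has no analysis section of its own.

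**The concern.** Anaemia prevalence and hospital cases of severe malaria are both named as endpoints in the protocol. Changing a definition between protocol and SAP is acceptable if the change is dated and explained. Here it is neither, and the SAP postdates the surveys. It describes the 2008-2010 fieldwork in the past tense and gives achieved numbers (2,889 children in 2008).

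Two things are at stake. A reader who looks for the anaemia result that the protocol promised will not find it, and will be unable to tell whether the cut-offs were chosen before or after the haemoglobin values were seen. And a result reported as an effect on severe malaria would describe a broader set of admissions than the protocol meant by that term.

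**Working it through.** **1. The protocol's power figure for Hb below 8 g/dL**

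Inputs from protocol section 2.3:
- control prevalence p0 = 0.15, halved to p1 = 0.075;
- k = 0.25 ("Assuming a coefficient of variation between clusters of 0.25");
- 150 children per zone less 20% loss, so m = 150 x 0.8 = 120;
- significance level 5%, taken as two-sided because the protocol does not say.

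From the section on phased introduction: 16 zones in Stratum A in year 1, of which 8 receive the intervention, so c = 8 per arm.

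The Hayes-Bennett formula for unmatched clusters is c = 1 + (z_alpha/2 + z_beta)^2 x V / (p0 - p1)^2, with V = p0(1-p0)/m + p1(1-p1)/m + k^2(p0^2 + p1^2).

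- V = 0.1275/120 + 0.069375/120 + 0.0625 x (0.0225 + 0.005625) = 0.001063 + 0.000578 + 0.001758 = 0.003398.
- (p0 - p1)^2 = 0.005625.
- Zones needed for 80% power: 1 + 7.849 x 0.003398/0.005625 = 5.7, so 6 per arm.
- Power with 8 per arm: sqrt(7 x 0.005625/0.003398) - 1.96 = 3.40 - 1.96 = 1.44, which gives 92.6%.

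| Variant | Power |
|---|---|
| t distribution, 14 df | 92.2% |
| without the +1 term | 95.3% |
| m = 150 | 94.8% |
| k = 0.30 | 86.7% |
| k = 0.35 | 79.5% |

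The stated 80% is not reproduced, but it errs on the safe side. The design met the target for the endpoint as the protocol defined it, so this calculation gives no reason for dropping the endpoint.

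**2. Whether the SAP's anaemia analyses recover it**

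Every child below 6 g/dL is also below 8, and every child below 8 is also below 11. The prevalence below 8 therefore lies between the two reported prevalences. The ratio between intervention and control areas is not bounded in that way: the ratio below 8 can lie outside the range of the ratios below 6 and below 11. A difference in mean haemoglobin does not give the proportion below 8 either. Only a direct analysis supplies the endpoint.

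**3. Severe malaria, side by side**

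| | Protocol | SAP |
|---|---|---|
| Event | admission for malaria with life-threatening features | admission with malaria as primary diagnosis |
| Diagnostic standard | WHO criteria | none stated |
| Parasitology | recorded on the form | not required |
| Confirmed and unconfirmed separated | not stated | no, although it is done for malaria incidence |

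Let w be the share of control-area admissions under the SAP definition that meet the protocol definition. The rate ratio for the SAP outcome is then w x RR(severe) + (1 - w) x RR(not severe). It equals the effect on severe malaria only if w = 1 or the two ratios agree. The documents give neither w nor the two ratios, so the size and direction of the difference cannot be calculated.

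**The case against.** The strongest defence is that nothing essential is lost. The protocol's objectives speak of anaemia prevalence without a cut-off, and the SAP still analyses anaemia at two levels as well as mean haemoglobin. Test-confirmed malaria, including cases at regional hospitals, has its own analysis. The trial also changed between the documents: 48 zones became 54 health posts, and the 2009 survey took children aged 4 to 123 months. The 15% prevalence was for children under five, so the power statement would not carry over intact in any case. All of this is fair and limits the point. It does not explain why the one cut-off that the protocol fixed twice is absent, or why the word severe was kept after the severity criteria went.

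A reader might infer more than the documents support:

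- *That the cut-offs were picked after seeing results.* The SAP's date allows this but does not show it. The documents do not say when the cut-offs were chosen or what had been looked at.
- *That the hospital label is biased in favour of the intervention because staff know the child's treatment.* The protocol has staff record details from the malaria card, but does not say that they see it before making the diagnosis. Any such bias depends on the share of admissions that are unconfirmed and the share of those whose label changes, and neither is given. A less specific definition can also dilute a real effect.
- *That Hb below 6 g/dL is hopelessly underpowered.* No prevalence is given for that cut-off. At an assumed fall from 2% to 1% with k = 0.25, the formula above gives 36% for 8 v 8 zones of 120 children. It gives 89% for the 2009 survey (54 health posts of 130 children) if these split 27 v 27, and the SAP does not state the split. No conclusion can rest on a range that wide.

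**Conclusion.** The point holds as two undocumented changes of definition. The protocol's anaemia endpoint, Hb below 8 g/dL, is not analysed, and the 80% power statement attaches to no analysis in the SAP. The SAP's severe-malaria outcome is broader than the protocol's and keeps a name that no longer fits.

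The size is moderate. Both outcomes are secondary, all-cause mortality is untouched, and anaemia and hospital malaria are still analysed under other definitions. The conclusion rests on the text alone. The recomputed power of about 93% assumes a two-sided 5% level and 8 v 8 zones, and shows only that the protocol's endpoint was adequately powered as planned. No claim is made about motive, about the direction of bias, or about the power of the new cut-offs.

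**What to change.** 1. Add Hb below 8 g/dL to the SAP as the protocol-specified anaemia endpoint, alongside Hb below 11, Hb below 6 and mean haemoglobin. The SAP reports haemoglobin for 2008 and 2009 and analyses it as a continuous value, so no new data are needed. The analysis methods already given for anaemia apply. Whether it should rank above the other cut-offs is a matter of preference and need not be settled.
2. Rename the SAP outcome as admissions to hospital with malaria as the primary diagnosis.
3. Report separately the admissions that meet the protocol's definition of severe malaria and have a positive slide or RDT, where the case report forms allow. The documents do not show that these forms were completed. If they were not, say so and report only the renamed outcome.
4. State when and why each definition changed, and whether outcome data by intervention area had been seen by then.

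The cost is SAP wording, one more anaemia analysis and a check of the hospital forms. The stricter severe-malaria outcome will have fewer events and a wider confidence interval.
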